## Results

As of February 10, 2022, the study is ongoing: 7 patients have been screened, and all were deemed eligible and enrolled in the study; 4 have completed baseline assessments.

## Discussion

This study’s design addresses both the short- and long-term effects of transcranial alternating current stimulation in a large study sample, by making comparisons with a sham treatment. Due to the COVID-19 pandemic, recruitment and enrollment slowed as a result of lockdowns imposed by the universities and health authorities.

The major limitation of the protocol is the lack of distinction between transcranial alternating current stimulation effects and cognitive training. A pilot study [14] showed cognitive improvement in patients with and without active transcranial alternating current stimulation treatment due to the combined effect of personal cognitive training. Thus, the independent effects of active transcranial alternating current stimulation treatment in comparison to sham transcranial alternating current stimulation are not discernible using this protocol. However, given the older age of study participants and often rapid degradation of cognitive function in dementia patients, it is the conscious effort of the research team to support brain stimulation even during sham treatments despite its confounding effect on results.

The study has been progressing as expected. Participants have found transcranial alternating current stimulation treatment to be agreeable and have adhered to outset eligibility criteria. Minor side effects, including fatigue and dizziness, have been appropriately addressed and managed during treatment.

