**Conclusions:**

We anticipate that transcranial alternating current stimulation will be a well-tolerated treatment, with no serious side effects and with considerable short- and long-term cognitive improvements.

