## Methods

### Experimental Design

This is a randomized, crossover, double-blind, placebo-controlled study. Participants with cognitive impairments are recruited at 1 of 2 sites (Manitoba and Alberta) and randomized into 2 groups, with stratification by age, sex, and cognitive level (measured with Montreal Cognitive Assessment [20]) for randomization. Group 1 participants receive active transcranial alternating current stimulation simultaneously with cognitive exercises. Group 2 participants receive sham transcranial alternating current stimulation simultaneously with cognitive exercises. Participants who cannot tolerate the application of transcranial alternating current stimulation and focus on the cognitive exercises at the same time are enrolled in a third group, in which they only receive cognitive exercises but otherwise follow the same protocol as those in group 1 and group 2. The outcomes of group 3 will be analyzed separately. Standard cognitive assessments are performed before and after treatment, as well as at a scheduled follow-up visit 3 months postintervention. Both participants and assessors remain blind to the type of treatment (active versus placebo) until the end of the study.

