### Treatment Protocol

Training for all groups occurs in-person over the course of 4 weeks, 5 days per week (excluding weekends); there is an 8-week wash-out period prior to group crossover. On each day, participants attend two 30-minute training sessions using an app (MindTriggers) with a 30-minute break in between. Assessments occur at baseline (week 0), postintervention (weeks 5 and 11), at a follow-up (week 16), and at a long-term follow-up (week 27). Assessment at week 11 is considered to be baseline for the second cycle. No crossover occurs for participants assigned to group 3 (Figure 1).

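### The article says long-term effects are compared with sham, but the only long-term visit (week 27) falls after crossover, when no randomized sham-only group remains

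*Protocol article*

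**What the plan says.** The claim is in the Discussion: the design "addresses both the short- and long-term effects of transcranial alternating current stimulation in a large study sample, by making comparisons with a sham treatment". The Abstract's Conclusions expect the treatment to be well tolerated, "with considerable short- and long-term cognitive improvements"; that is an expectation and does not mention sham.

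The schedule is in Treatment Protocol: "Assessments occur at baseline (week 0), postintervention (weeks 5 and 11), at a follow-up (week 16), and at a long-term follow-up (week 27"). The same section adds: "Assessment at week 11 is considered to be baseline for the second cycle". Week 11 therefore has two roles, as a postintervention visit for cycle 1 and as the starting point of cycle 2. Experimental Design announces "This is a randomized, crossover, double-blind, placebo-controlled study" and describes follow-up "as well as at a scheduled follow-up visit 3 months postintervention", which fits week 27 if the second cycle ends at about week 15.

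Treatment Protocol also states that "there is an 8-week wash-out period prior to group crossover". Group 3 consists of people who could not tolerate stimulation. They receive cognitive exercises only, do not cross over and are analyzed separately (Experimental Design, Recruitment, Treatment Protocol).

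**The concern.** A sham-controlled statement about a time point needs a randomized group that has had sham and not active treatment by then, or an assumption that the earlier active treatment no longer matters. Cycle 2 starts from week 11, so the crossover comes before both week 16 and week 27. At week 27, group 1 has had active then sham, and group 2 has had sham then active. What still differs between them is the order of treatment and the time since active treatment.

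A week-27 comparison of the two groups would look null exactly when the benefit lasts, and could then be read as evidence against durability. A before-after change at week 27 has no control for practice or disease decline, and the Discussion itself refers to often rapid decline in this population. The Introduction says the pilot did not analyze the placebo effect and that this trial should address such shortcomings. For long-term effects the schedule does not allow that.

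**Working it through.** **1. The plan's own figures.** Sample Size Estimation gives a difference of 20, an SD of 38, 80% power and 5% significance (taken as two-sided). The normal formula gives 2 × [38 × (1.960 + 0.842)/20]² = 56.7 per group. The t-test version gives 57.6, rounded up to 58, which matches the plan. Of 75 enrolled, 75 × 0.80 × 0.95 = 57 tolerate stimulation and complete, that is 28 and 29 per sequence.

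**2. Exposure by visit.** The cycle dates are inferred from the assessment weeks: cycle 1 in weeks 1–4, cycle 2 in about weeks 12–15.

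| Visit | Group 1 has had | Group 2 has had | Randomized sham-only group? |
|---|---|---|---|
| Week 5 | active | sham | yes |
| Week 11 | active, ended about 7 weeks before | sham | yes, for the last time |
| Week 16 | active, then sham | sham, then active | no |
| Week 27 | active, ended about 23 weeks before | active, ended about 12 weeks before | no |

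**3. What the week-27 group contrast estimates.** Let e(t) be the effect t weeks after active treatment ends. Both groups have had two cycles of cognitive training, so the group difference (group 2 minus group 1), as a level or as change from week 0, is e(12) − e(23). The quantity of interest is e(12).

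For illustration, assume e(t) = 20 × 0.5^(t/h). The half-life h is not in the documents, so a range is shown.

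| Half-life h (weeks) | True e(12) | e(23) | Week-27 contrast | Share of e(12) |
|---|---|---|---|---|
| 4 | 2.5 | 0.4 | 2.1 | 85% |
| 8 | 7.1 | 2.7 | 4.3 | 61% |
| 12 | 10.0 | 5.3 | 4.7 | 47% |
| 26 | 14.5 | 10.8 | 3.7 | 25% |
| 52 | 17.0 | 14.7 | 2.3 | 14% |
| permanent | 20 | 20 | 0 | 0% |

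(Values are rounded separately.) The share recovered falls steadily as the effect becomes more durable.

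**4. Sensitivity to the wash-out conflict.** A cycle ending at week 4 plus 8 weeks of wash-out reaches week 12, which does not fit a second-cycle baseline at week 11 and a 4-week cycle completed before week 16. If cycle 2 instead ended at week 16, group 2 would be 11 weeks past active treatment at week 27. With h = 12 the contrast is then 20 × (0.5^(11/12) − 0.5^(23/12)) = 10.6 − 5.3 = 5.3, half of the true 10.6. The conclusion does not change.

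**5. Precision at week 11.** The 95% half-width for group 1 versus group 2, unadjusted, is 2.004 × 38 × √(1/28 + 1/29) = 20.2 points.

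**The case against.** **Week 27 is a period-2 active-versus-sham contrast.** About 12 weeks after cycle 2, group 2 has just had active and group 1 sham, and the Analysis section plans to examine carryover. This stands as a formal point: the contrast is valid if carryover is negligible. But a benefit that lasts is carryover, so the condition denies the effect being looked for.

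**Use change from the second-cycle baseline.** This is the strongest form, since week 11 is the stated baseline for cycle 2. The contrast becomes e(12) + [e(7) − e(23)]. It does not vanish for a permanent effect, and it is right if the effect is wholly gone by week 11 or does not fade at all between 7 and 23 weeks. In between it overstates. With h = 12 it gives 10.0 + 13.3 − 5.3 = 18.0 against a true 10.0, because two-thirds of group 1's effect is still in its week-11 baseline. Group 1's own change over that interval mixes fading with decline and the sham cycle, so the trial cannot isolate the correction.

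**Week 11 is already available.** Correct. It is listed as postintervention, and the planned repeated-measures model can use it. A reader might infer that the plan uses week 11 only as a baseline; the schedule does not support that.

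**Nothing confirmatory depends on week 27.** Also correct. Hypothesis 2 concerns the time immediately after the intervention, hypotheses 1 and 3 name no long-term time, and neither the primary outcomes nor the sample size singles out week 27.

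**Low power is mainly a matter of sample size.** Partly so. With SD 38 and 28.5 per group, even an undiminished 20-point parallel-group difference has only about 50% power. The argument here therefore rests on what the contrast estimates. The article specifies no week-27 test whose power could be criticised.

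**Conclusion.** The point holds with moderate severity. The Discussion credits the design with a sham-controlled long-term comparison that its schedule does not provide: the last visit with a randomized sham-only group is week 11, about 6 to 7 weeks after cycle 1. The week-27 group contrast measures fading between about 12 and 23 weeks. Its shortfall is roughly half of the true effect at a 12-week half-life, three-quarters at 26 weeks and all of it for a permanent effect.

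The sizes rest on assumed exponential decay and on week counts inferred from the assessment schedule. That there is no sham-only group at week 27 follows from the crossover itself.

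Two stronger readings are not supported. A reader might infer that everyone has had active stimulation by week 27; group 3 has not received the stimulation treatment, although it cannot serve as a sham control. A reader might also infer that the trial's main comparison is compromised; it is not on this ground, because the within-cycle comparisons and the stated hypotheses do not depend on week 27.

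**What to change.** - Specify group 1 versus group 2 at week 11, adjusted for week 0, as the sham-controlled off-treatment comparison, and describe it as about 6 to 7 weeks after treatment. Report its precision openly: about ±20 points unadjusted, as large as the planned difference. Adjustment for week 0 will narrow this by an amount the documents do not allow one to state.
- Report week 27 as descriptive follow-up or as a comparison of treatment sequences, and say that a null group difference there is not evidence against a lasting effect.
- Limit the Discussion's claim of sham-controlled effects to data through week 11 and the within-cycle comparisons, and list the loss of the sham control at week 27 among the limitations.
- Reconcile the stated 8-week wash-out with the assessment weeks, so that the time since treatment at weeks 11, 16 and 27 is unambiguous.

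The cost is revised wording and one named analysis of data already being collected. No visits or participants are added. The price is a narrower claim, supported by an imprecise estimate.

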## Appendix

Multimedia Appendix 1 Peer-review reports (1) from Mitacs Accelerate - Funded Internship Projects (Canada).

Multimedia Appendix 2 Peer-review reports (2) from Mitacs Accelerate - Funded Internship Projects (Canada).

Multimedia Appendix 3 CONSORT-eHEALTH checklist (V 1.6.1).

## Abbreviations

ADAS: Alzheimer Disease Assessment Scale
